## 1003 **9 Participant Completion and Withdrawal**

### 1004 **9.1 Participant Completion**

1005 Participants are considered to have completed the study if they complete 12 weeks of dosing.

### 1006 **9.2 Participant Withdrawal by the Investigator**

1007 Patients will be withdrawn from the study by the Investigator, prior to completion of treatment,  
1008 under the following conditions:

- 1009 • Non-compliant with study medication for seven consecutive days
- 1010 • Development of a serious adverse event assumed to be associated with the study  
1011 medication
- 1012 • Cessation of effective contraception or confirmed pregnancy
- 1013 • Continual inability to provide informed consent.

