## 7.5 Randomisation Procedure

Participants will be randomised once written consent has been obtained and the baseline assessments have been completed. Participants will be randomised to one of the treatment groups, using blocks of 4 via a computer-generated randomization table. Randomisation will be stratified by five sites (a) Metro North HHS, (b) Metro South HHS, (c) West Moreton HHS, (d) Gold Coast HHS, and (e) Children's Health Queensland HHS. Participants will receive either active treatment or placebo in a 1:1 ratio.

The investigational products will be manufactured in accordance with current Good Manufacturing Practice (GMP) in a suitable TGA licensed facility. This same company (Pharmaceutical Packing Professionals) will hold the randomisation code, and provide a 24 hour

1800 number to unblind participants if required. Participants will be randomised strictly using a chronological process. Participants will be allocated a unique identification number which will be linked to the specific site number. If a participant withdraws from the study then the participant number will not be re-used nor will the participant be allowed to re-enter the study.

The randomisation will be double-blind. An independent Biostatistician will generate the randomisation list which will be provided to the manufacturer. The independent manufacturer will hold the closed randomisation list and be the only one who has the ability to unblind. In the case of emergency where it is crucial the medical staff knows whether the participant is on sodium benzoate or placebo, participants will be provided with contact information (i.e. 24 hour 1800 number) for unblinding.

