## **7.7 Blinding and Unblinding Procedure**

All medication will be blinded to the study personnel, research pharmacist and the patient. Sodium benzoate and placebo capsules will be identical in packaging, appearance, colour and taste. Treatment allocations will not be disclosed to the Investigator or any study personnel before the database is locked, unless in the case of an emergency requiring unblinding. Unblinded participants will be withdrawn from the study.

Only in the event of a medical emergency which the investigator feels cannot be adequately managed without knowing the identity of the study medication, will the treatment code be unblinded for a particular participant. This will be done by the independent manufacturer via the 24 hour 1800 number. All cases of emergency unblinding will be documented on a Serious AE Form and reported to The University of Queensland, (Sponsor) within 24 hours.

After the completion of all participants in the study (last patient last visit), participants will be notified which arm of the study they took part in.

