## **11 Data Analysis and Statistical Considerations**

### **11.1 Hypotheses**

Those participants allocated to the active arm (1000mg (500mg BD)) Sodium Benzoate treatment will have significant reductions in PANSS total score at week 12 compared to individuals taking placebo.

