### **11.4 Statistical Analysis**

All data will be analysed using SAS 9.4. We will compare demographic and clinical differences between the groups at baseline (Fisher exact test for nominal variables and Mann-Whitney test or independent sample  $t$  test for continuous variables). Efficacy will be assessed according to standard Intention to Treat (ITT) analytic procedures (i.e. for those who do not complete the 12 week study period, we will carry forward their last observation on the study outcomes). Mean changes in clinical assessment will be assessed using mixed-model repeated-measure (MMRM) methods with treatment, week, and treatment-week interaction as fixed effects and intercept as the only random effect; baseline value will be the covariant. The MMRM analyses will be performed using the SAS PROC Mixed procedure.  $P$  values will be based on 2-tailored tests with significance levels of 0.05.

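### Withdrawal from the study, rather than from study drug alone, builds in week-12 PANSS data whose absence depends on adherence, related SAEs, pregnancy or unblinding

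*Protocol*

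**What the plan says.** Protocol section 9.2 states: "Patients will be withdrawn from the study by the Investigator, prior to completion of treatment". One listed condition is "Non-compliant with study medication for seven consecutive days". The others are a serious adverse event assumed to be linked to study medication, stopping contraception or confirmed pregnancy, and continuing inability to give informed consent.

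Section 7.7 adds: "Unblinded participants will be withdrawn from the study". Section 8.10 names stopping the medication and being withdrawn from the study as two separate consequences of pregnancy, so the protocol does not use the one as loose wording for the other.

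Section 9.1 defines completion by treatment: "Participants are considered to have completed the study if they complete 12 weeks of dosing". Section 7.5 says of a participant who withdraws that the number will not be re-used, "nor will the participant be allowed to re-enter the study".

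The primary hypothesis in section 11.1 is that the active arm "will have significant reductions in PANSS total score at week 12 compared to individuals taking placebo". Section 11.4 says: "Efficacy will be assessed according to standard Intention to Treat (ITT) analytic procedures". It explains this as follows: "for those who do not complete the 12 week study period, we will carry forward their last observation on the study outcomes". The same section then specifies a mixed model for repeated measures (MMRM) with a random intercept and baseline as covariate.

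**The concern.** An intention-to-treat comparison at week 12 is best supported by week-12 ratings on everyone randomised, whether or not they kept taking capsules. Here the protocol ends study participation because of events that follow randomisation: adherence, a related serious adverse event, pregnancy, unblinding. The resulting gaps are unlikely to be random, since people who stop taking capsules for a week may well differ in prognosis from those who continue. Some of them may still be willing to be rated, so part of the loss is avoidable.

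A statistical analysis plan can choose how to model missing ratings, but it cannot recover ratings that were not taken. Whether visits continue after drug is stopped is a protocol decision.

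**Working it through.** **1. Is there any provision for a later rating?**

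- Section 9 has no early-termination visit and no assessments off drug.
- Table 1 schedules PANSS at screening, baseline and weeks 2, 4, 6, 8, 10 and 12, with no column for participants who have left early.
- The follow-up described beyond the scheduled contacts (sections 8.8 and 8.11) concerns adverse events only.
- Section 11.4 plans carry-forward for non-completers, which fits the expectation that no later rating will exist.

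**2. The plan's own sample size.** Inputs from section 11.3: difference 7, SD 14.3, power 0.80, alpha 0.05 (two-sided in section 11.4), attrition 15%.

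- n per arm = 2 × (1.960 + 0.842)² × (14.3/7)² = 65.5, so 66 per arm and 132 in all. This matches the protocol.
- 132 / 0.85 = 155.3, so 156; the protocol rounds to about 160.
- 160 randomised tolerates 1 − 132/160 = 17.5% loss before falling below 132.

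The sample size is not in error.

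**3. Power against loss of week-12 data.** Normal approximation, m = 80 × (1 − loss) per arm, power = Φ(7 / (14.3 × √(2/m)) − 1.96). The loss rates other than the protocol's 15% are assumptions.

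| Loss | m per arm | Power |
|---|---|---|
| 15% | 68 | 0.814 |
| 17.5% | 66 | 0.803 |
| 20% | 64 | 0.791 |
| 25% | 60 | 0.765 |
| 30% | 56 | 0.736 |

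**4. Would rating people off drug restore power?** Suppose all 160 are rated at week 12 and a share f of the active arm keeps no benefit (an assumption). The difference becomes 7 × (1 − f).

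| f | Difference | Power at 80 per arm |
|---|---|---|
| 5% | 6.65 | 0.837 |
| 10% | 6.30 | 0.796 |
| 15% | 5.95 | 0.749 |
| 20% | 5.60 | 0.697 |

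A smaller recovery shows the same thing. Raising the rated number from 68 to 76 per arm at a full 7 units moves two-sample t power from 0.809 to 0.850. But the 8 added active-arm participants are off drug. If they keep no benefit, the difference is 7 × 68/76 = 6.26 and power is 0.765, below the starting value.

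**5. Size of a possible bias.** If withdrawn participants would score g points worse at week 12 than completers, the completers-only difference departs from the all-randomised difference by g × (difference in withdrawal rates). All values below are assumptions.

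- 10% against 20%, g = 7: 7 × 0.10 = 0.7 points.
- 10% against 20%, g = 14.3: 14.3 × 0.10 = 1.43 points.
- Equal rates and equal gaps: 0.

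This describes a completers-only comparison. Carry-forward or MMRM would give a different error, governed by their own assumptions.

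**The case against.** A reader might infer that week-12 scores will never be collected for these participants and that intention to treat therefore cannot be done. The document supports neither. It provides no rating after withdrawal but does not forbid one. Section 11.4 keeps non-completers in by carry-forward, and the MMRM can use the fortnightly PANSS scores already obtained, so participants with post-baseline data can be analysed as allocated.

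A reader might also infer that following everyone up buys power. Step 4 shows this depends on how much benefit remains after drug is stopped, which the protocol does not give; power could fall.

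The numbers affected are also unknown. Section 11.3 predicts 15% attrition without giving causes, and people who withdraw consent or are lost to contact would not be recovered by any change here. Section 7.7 reserves unblinding for medical emergencies, so it is probably rare. Nothing in the protocol predicts different withdrawal rates by arm, and the earlier schizophrenia trial described in sections 1.3 and 7.2 found no significant adverse-event difference from placebo.

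These points limit the size of the concern. They do not remove it: for anyone withdrawn under these rules before week 12, the analysis relies on an assumption that cannot be checked from the data. Carry-forward assumes no change after the last visit, the MMRM assumes missing at random, and section 11.4 names both without saying which governs.

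**Conclusion.** The point holds as a design weakness. Sections 7.7, 8.10 and 9.2 end study participation, section 9.1 measures completion by dosing, and no PANSS off drug is provided. The plan thus creates missing week-12 outcomes that depend on post-randomisation events, and its intention-to-treat result rests on imputation or modelling for those participants instead of observed ratings.

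The size cannot be fixed from the document, because the number meeting these rules is not stated. Under the assumed rates and gaps in step 5, the shift in a completers-only comparison runs from 0 to about 1.4 points, against the 7-unit target difference. The planned 66 per group and about 160 randomised stand. The case for change is reduced bias and a clearly defined treatment comparison, not power.

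**What to change.** Leave all rules for stopping study medication as they are, and separate stopping study drug from leaving the study in sections 7.7, 8.10, 9.1 and 9.2.

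- Invite participants who stop drug, and who have neither withdrawn consent nor lost capacity to consent, to the remaining scheduled assessments, at minimum the week-12 PANSS.
- Include those ratings in the intention-to-treat analysis as randomised.
- Flag ratings made after unblinding and run a sensitivity analysis without them, since PANSS is rated by study staff.
- Record completion of assessments separately from completion of dosing.
- Reconcile section 7.5, so that the bar on re-entry does not block continued assessment.
- Reconcile section 16.13, which makes anyone treated in deviation from the protocol ineligible for analysis. Left as it is, it conflicts with intention to treat and could exclude the very scores collected.

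The cost is a short amendment, which under section 16.11 needs ethics committee approval and approval of any revised consent form, plus attendance at visits already in the schedule. The treatment difference may be diluted by participants off drug; that should be stated openly and no power gain claimed.

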### 1014 **9.3 Participant Withdrawal**

1015 All participants have the right to withdraw consent at any time without prejudice and this will not  
1016 affect their ongoing care. This will be clearly discussed during the consenting process. If a  
1017 participant decides to withdraw consent we will complete a revocation of informed consent form.

### 1018 **9.4 Early Termination of the Study**

1019 The study may be terminated prematurely by the Coordinating and or Principal investigator or  
1020 his/her designee and the sponsor if:

- 1021 • The number and/or severity of adverse events justify discontinuation of the study.
- 1022 • New data becomes available which raises concern about the safety of the study drug, so that  
1023 continuation might cause unacceptable risks to participants.

1024

1025 After such a decision, the Investigator or designee will contact all participants promptly, and  
1026 written notification of study termination will be sent to the Reviewing Ethics Committee and  
1027 relevant Governance Offices. A study closure advice will also be sent to the TGA on the approved  
1028 form. The Australian Clinical Trial Registry entry will also be updated accordingly.

## 1029 **10 Case Report Form (CRF)**

1030 A Case Report Form (CRF) will be completed for each study participant summarising all clinical  
1031 screening and study data that is to be provided to the University of Queensland (Sponsor) for data  
1032 analysis. In the CRF, participants will only be identified by their participant number in order to  
1033 retain participant confidentiality.

1034

1035 The completed Case report Forms (CRF's) will be retained by the Investigators for a period of at  
1036 least 15 years or the maximum time frame as determined by local regulations, whichever is the  
1037 longest.

1038

## **11 Data Analysis and Statistical Considerations**

### **11.1 Hypotheses**

Those participants allocated to the active arm (1000mg (500mg BD)) Sodium Benzoate treatment will have significant reductions in PANSS total score at week 12 compared to individuals taking placebo.

### **11.2 Endpoints**

#### **11.2.1 Primary**

12 week treatment of 1000mg (500mg BD) Sodium Benzoate treatment improves the Positive and Negative Syndrome Scale (PANSS) total score compared to individuals taking placebo.

#### **11.2.2 Secondary**

12 week treatment of 1000mg (500mg BD) Sodium Benzoate treatment improves Positive and Negative Syndrome Scale (PANSS) subscales, Global Assessment of Function (GAF), Australian Quality of Life Scale (AQOL), The Activity and Participation Questionnaire (APQ6), Clinical Global Impression (CGI) and Hamilton Depression rating Scale-17items (HDRS) compared to individuals taking placebo.

#### **11.2.3 Tertiary**

Sera markers related to D-alanine, L-alanine, D-serine, L-serine, glycine and glutamate will change from baseline to endpoint in those on active treatment.

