### 2.3 Tertiary (Exploratory) Objectives

To explore if sera markers related to D-alanine, L-alanine, D-serine, L-serine, glycine and glutamate change from baseline to endpoint in those on active treatment.

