## 6.1 Biomarkers

The Director of the National Institute of Mental Health ([name]) has recently urged that clinical trials in mental health need to be enriched for biomarkers related to the proposed “target” of the intervention. This will be achieved by collecting a 25ml blood sample via venipuncture at both baseline and final patient interviews. A portion of this sample will be used to assess the concentration of key analytes in the pathways related to sodium benzoate. D-amino acid oxidase is needed to catabolize (break down) D-alanine. D-alanine can be measured in sera with High Performance Liquid Chromatography HPLC. In addition; we can measure related species that could be altered by the intervention, including L-alanine, D- and L-serine, glycine and glutamate. The investigators have suitable equipment and laboratory skills to assess these molecules. Collecting these measures will allow us to assess if sodium benzoate impacts on these analytes in the peripheral blood.

The remainder of the blood sample will be stored indefinitely for future research. However, future studies involving the stored blood samples will require approval from a Human Research Ethics Committee. There is strong justification to explore the association between common variants in genes involved in the glutaminergic pathways (benzoate impacts on analytes that are involved in these systems). For example, the recently published study in Nature identified 108 loci linked to

586 risk of schizophrenia. Several of these are linked to genes in these same pathways that are  
587 related to the action of sodium benzoate. Of particular relevance to the current protocol, common  
588 variants in serine racemase (SRR) were significantly associated with an increased risk of  
589 schizophrenia – this enzyme is upstream of DAAO, and involved in the metabolism of serine. While  
590 the study of the current sample size will not have sufficient power to test the impact of common  
591 variants in these genes versus outcomes in this study (the effect sizes for all SNPs linked to  
592 schizophrenia are small, between 1.1 and 1.4), we wish to bank this material down for future  
593 collaborative studies. This feature of the study will be clearly outlined in the consent form, and  
594 participants will be informed that DNA and sera samples may be used in future years by national  

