## **6.3 Study Restrictions**

There are no restrictions to participants during the study in terms of concomitant medications, exercise or ambulation. While sodium benzoate is often added to vitamin C rich products such as orange juice, there has been concern that sodium benzoate may interact with high dose vitamin C formulations to produce benzene (a known carcinogen). There is an absence of clear guidance on this matter, thus for the purposes of this protocol, we will adopt a conservative stance and require patients to avoid using vitamin C formulations that contain more than 500 mg/day (multivitamin tablets have lower doses of vitamin C and can be continued during the study, as can citrus fruits and food products that contain vitamin C naturally).

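### The exploratory biomarker objective and endpoint are worded as change in the active arm only, although section 6.1 asks about the effect of sodium benzoate and blood is scheduled in both arms

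*Protocol*

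**What the plan says.** Section 11.2.3 gives the tertiary endpoint as "Sera markers related to D-alanine, L-alanine, D-serine, L-serine, glycine and glutamate will change from baseline to endpoint in those on active treatment". Section 2.3, headed as exploratory, has the matching objective: whether the markers "change from baseline to endpoint in those on active treatment". Neither names a comparator.

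The other efficacy endpoints do. Section 11.2.1 asks whether treatment "improves the Positive and Negative Syndrome Scale (PANSS) total score compared to individuals taking placebo". The secondary list in section 11.2.2 ends "Clinical Global Impression (CGI) and Hamilton Depression rating Scale-17items (HDRS) compared to individuals taking placebo". Sections 2.1 and 2.2 word the primary and secondary objectives in the same comparative way.

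Section 6.1 gives the purpose of the biomarkers: "Collecting these measures will allow us to assess if sodium benzoate impacts on these analytes in the peripheral blood". It plans for "collecting a 25ml blood sample via venipuncture at both baseline and final patient interviews", with no restriction by arm, and Table 1 shows one common schedule with blood at weeks 0 and 12. Section 6.1 also lets a person decline sampling and stay in the trial, and the risk table in section 8.12 allows refusal at any stage.

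Section 6.3 sets no restrictions "to participants during the study in terms of concomitant medications, exercise or ambulation", apart from a limit on vitamin C formulations. Section 11.4 states the mixed model, with its treatment and treatment-by-week terms, for the clinical assessments. It does not mention the sera markers.

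**The concern.** The aim in section 6.1 is causal, and a before-after change in one arm does not answer a causal question. Participants are within two years of onset, receive individualised routine care and may change other medication. Analyte levels could therefore move over 12 weeks for reasons unrelated to the study drug. Diet, or assay and storage effects, could add to this if present. A shift common to both arms cancels in a randomised comparison and stays in full in a within-arm change.

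These analytes are the only scheduled measures tied to the drug's proposed mechanism. A reported change in the active arm would be used to interpret the PANSS result, whether positive or null. If placebo moved equally, that interpretation would be wrong, although the trial had scheduled the samples needed to show it.

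**Working it through.** **1. The wording, side by side.**

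| Level | Sections | Contrast stated |
|---|---|---|
| Primary | 2.1, 11.2.1 | against placebo |
| Secondary | 2.2, 11.2.2 | against placebo |
| Tertiary | 2.3, 11.2.3 | baseline to endpoint, active arm only |

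The active-only wording stands in both the objective and the endpoint, so a slip in a single place is unlikely. Section 6.1 and Table 1 schedule the samples that a comparison with placebo would need.

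**2. The plan's own figure.** The protocol gives no calculation for the biomarkers. Its PANSS sample size (section 11.3: difference 7, SD 14.3, two-sided 0.05, power 0.80) reproduces:

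n per group = 2 × 14.3² × (1.960 + 0.842)² / 7² = 65.5, rounded up to 66, so 132 in total. Dividing by 0.85 for 15% attrition gives 156, against the stated figure of approximately 160.

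This point does not depend on that calculation. It only supplies the numbers in the arms.

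**3. Illustration of a shared drift.** Inputs:
- Active arm randomised: 160 / 2 = 80 (1:1 allocation, section 7.5).
- Active completers: 80 × 0.85 = 68 (attrition from section 11.3).
- Two-sided level 0.05 (section 11.4).
- Drift s, in SDs of the change score, the same in both arms: **assumed**, because the protocol gives no analyte mean, SD or drift.
- True drug effect: zero.

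A paired t-test on n active pairs has non-centrality s × √n with n − 1 degrees of freedom. For n = 68 and s = 0.2 this is 0.2 × 8.246 = 1.65. For s = 0.3 it is 2.47. The probability of a significant within-arm change is then:

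| Shared drift s | 68 pairs | 40 pairs |
|---|---|---|
| 0 | 5% | 5% |
| 0.1 | 12.8% | 9.5% |
| 0.2 | 36.9% | 23.5% |
| 0.3 | 68.4% | 45.7% |
| 0.4 | 90.2% | 69.4% |

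The 68 is an upper figure, since it supposes that every active completer gives both samples. The 40 is an arbitrary lower figure, chosen to show what optional sampling could do.

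**4. The between-arm comparison.** If the drug effect is δ and the shared drift is s, the expected difference in mean change is (δ + s) − s = δ. With δ = 0 the test rejects 5% of the time for every s in the table. With 66 per arm it has 80% power for a standardised difference of (1.960 + 0.842) × √(2/66) = 0.49 SD of change. That is a best case for precision, again because sampling is optional.

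**The case against.** The strongest reply is that no test is stated. Section 11.2.3 is one line saying where change is expected, and it also fits a prediction that active patients change and placebo patients do not. Methods for an exploratory laboratory measure are commonly left to a statistical analysis plan, which is not at hand. This stands in part: the paired t-test above is an illustration and not something the protocol prescribes. It does not remove the point, because the protocol itself fixes a single-arm hypothesis in two places. An analysis plan that follows it inherits the problem, and one that departs from it conflicts with the protocol.

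Three stronger readings are tempting, and the document does not support them:
- *The placebo samples will be discarded, so attribution is impossible.* Nothing says so. Section 6.1 plans to assay part of the sample without restriction by arm. The planned data can support the randomised contrast; only the stated objective and endpoint fail to ask for it.
- *Regression to the mean will produce a spurious change.* No analyte level is an entry criterion. Section 4.2 selects on PANSS, and the protocol gives no link between PANSS and the serum levels.
- *The 37% and 68% are this trial's error rates.* They follow from assumed drifts. At zero drift the rate is 5%.

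It is also fair to say that the objective is exploratory and drives no sample size, efficacy or safety conclusion.

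**Conclusion.** The point holds as a wording fault in an exploratory objective and endpoint. Sections 2.3 and 11.2.3 state a within-active-arm change, which cannot answer the question that section 6.1 asks. Sampling is scheduled in both arms and the rest of the protocol uses placebo as comparator.

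The size is conditional. If both arms drift by 0.2 to 0.3 SD of the change score, 68 active pairs would give a significant within-arm change in about 37% to 68% of trials with no drug effect. With 40 pairs the range is about 23% to 46%. These figures assume the drift, and the 68 assumes complete sampling among completers. Whether any such drift will occur cannot be judged from the protocol. The primary conclusion is unaffected. The change is worth making because it is cheap and makes the stated aim answerable.

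**What to change.** Reword sections 2.3 and 11.2.3 along these lines: *difference between sodium benzoate and placebo in the week-12 serum concentration of each analyte, adjusted for its baseline value*. Report within-arm changes descriptively.

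ANCOVA with site, the stratification factor, as a covariate is one suitable model. The essential change is the comparison with placebo; the model itself can be left to the analysis plan. Because sampling is optional, the number of participants with both samples should be reported by arm.

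No new visits or blood draws are needed. The only cost is assaying the placebo samples, if that was not already intended.
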